### Study variables

Baseline variables regarding efficacy and safety are described in Table 
3 and were measured as appropriate during the follow-up visits.

**Table 3 Tab3:** **Study variables**
^**a**^

Category	Variables
Demographic data	Sex and age
Comorbidities	COPD, diabetes, obesity, kidney failure, hepatic disease, AIDS, cancer, leukemia, connective tissue disease, cerebrovascular disease, other comorbidities
Previous vaccinations	Influenza vaccination (seasons 2011–2012 and 2010–2011), influenza A H1N1 (2009) vaccination, pneumococcal conjugate vaccination, other immunizations
Solid organ Transplant	Date, organ, immunosuppressive treatment, graft rejection history, use of monoclonal antibodies
Influenza infection records	Confirmed influenza infection in previous season, confirmed influenza infection after study treatment, influenza severity, influenza treatment, influenza treatment outcome, date of recovery
Immune response	Seroconversion and seroprotection rates (GMT, GMR), influenza virus–specific memory A- and B-cell responses, confirmed influenza infection during follow-up
Adverse events	Dates, progress, intensity, expectability, causality, progress, toxicity degree
Concomitant treatments	Indication, dose, frequency, administration route, start and end dates

^a^COPD, Chronic obstructive pulmonary disease; GMR, Geometric mean ratio; GMT, Geometric mean titers.

### Outcome measures

Seroconversion rate was the primary end-point variable of the study. Microneutralization assays were performed to quantify neutralizing antibody titers against the two influenza A strains and the influenza B strain. Immunological response and vaccination efficacy were based on the following international criteria: (1) geometric mean titers (GMT; mean antibody titer in the group of vaccinated individuals), (2) seroprotection rate (percentage of patients with antibody titers ≥1:40), (3) seroconversion rate (percentage of participants with four fold increase in antibody titers from baseline) and (4) geometric mean ratio (GMR; seroconversion factor postvaccination compared with prevaccination). Neutralizing antibody titers were evaluated at 5, 10 and 15 weeks and 1 year after influenza vaccination. Cellular immune response to vaccination was determined by quantifying influenza-specific CD4+ and CD8+ memory cells at baseline, 15 weeks and 1 year after influenza vaccination. For each treatment arm, clinical efficacy was assessed by evaluating the episodes of confirmed influenza infection during a 1-year follow-up period. The safety endpoints at each evaluation time frame were rejection episodes, hospitalization, graft loss, mortality, incidence of AEs and severe AEs and rates of discontinuation due to AEs.

In order to study in-depth the immune response to influenza vaccination in SOT recipients, we will also explore other genetic and biological outcomes in the collected samples. Genetic expression patterns of immune response and anti–human leukocyte antigen levels induced by influenza vaccination will be analyzed as ancillary outcomes.

### Sample size calculation

Sample size was calculated using the results of a Spanish multicenter study in which SOT recipients received a single dose of seasonal influenza vaccination during the 2010–2011 season
[27]. In that study, seroconversion rates against influenza A(H1N1) 2009, influenza A(H3N2) and influenza B were 77%, 67% and 67%, respectively. According to these estimates, we calculated our sample size according to the following criteria:

To achieve a 95% confidence level (significance level of 5%) and 80% statistical power to observe differences in testing the null hypothesis (H0)p1 = p2 using a χ^2^ bilateral test in two independent samples.To obtain an increase in the primary endpoint of 10% (increased percentage of seroconversion rate in the experimental arm), which is considered clinically relevant in the literature. According to this criterion, we would expect to achieve 77% and 87% seroconversion rates in the control and experimental arms, respectively.To estimate a 10% dropout rate per arm.

According to these premises, and using a 1:1 ratio of experimental units to controls, the minimum number of patients was set at 231 units in each treatment arm, with a total of 462 evaluable participants to be recruited for the study. Taking into account the estimated loss percentage, the total number of patients needed for the study was set at 514 (257 participants per treatment arm). Sample size was calculated using the online Simple Interactive Statistical Analysis calculator
[29].

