## Abstract

**Background:**

Despite administration of annual influenza vaccination, influenza-associated complications in transplant recipients continue to be an important cause of hospitalization and death. Although influenza vaccination has been proven to be the most effective measure to reduce influenza infection after transplantation, transplant recipients are still vulnerable to influenza infections, with lower serological responses to vaccination compared to the general population. In order to assess the efficacy and safety of an alternative immunization scheme for solid organ transplant recipients, the TRANSGRIPE1-2 Study Group aimed to test a booster dose administration 5 weeks after the standard vaccination. The primary objective of this trial was to compare short-term and long-term neutralizing antibody immunogenicity of a booster dose of influenza vaccination to the standard single-dose immunization scheme. Secondary objectives included the evaluation of the efficacy and/or safety, cellular immune response, incidence of influenza infection, graft rejection, retransplant and mortality rates.

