[27]. This may be due either to immunosuppressive regimens that, although critical for preventing acute rejection, deplete the adaptive arm of the immune system, or to seasonal vaccine strain modifications that may decrease immunogenicity. A booster dose given some weeks after the standard dose may elicit a long-lasting antibody response, thus producing better protection in current and subsequent influenza seasons. The booster strategy has been tested in several studies involving different types of transplant recipients, but the results are as yet inconclusive
[28]. In addition, no randomized controlled trial has addressed this issue to date.

The TRANSGRIPE 1-2 study is a publicly funded, phase III, parallel-group, randomized clinical trial for the evaluation of the safety and efficacy of a booster dose of trivalent inactivated seasonal influenza vaccine administered 5 weeks after seasonal influenza vaccination compared to a single dose of the vaccine administered to SOT recipients. In the present study, we hypothesized that the efficacy of seasonal trivalent inactivated influenza vaccination might be significantly increased in SOT recipients by administering a second booster dose 5 weeks after the standard single-dose vaccination.

The primary objective of the present clinical trial is to compare short-term immunogenicity by measuring neutralizing antibodies after a booster dose versus a standard single dose of influenza vaccine in SOT recipients.

The following are the secondary objectives of the trial:

To compare the long-term immunogenicity of two doses versus a standard single-dose of influenza vaccineTo compare short-term and long-term influenza-specific T-cell immune responses among patients within both treatment armsTo determine the clinical effectiveness of the experimental vaccination scheme, measuring the incidence of confirmed influenza infectionTo establish a safety intervention by analyzing incidence of adverse events (AEs), mortality and outcomes such as graft rejection

Moreover, TRANSGRIPE1-2 trial bears two associated biological substudies in patients who provided specific consent for additional investigations.

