**Figure 1 Fig1:**
[figure not shown]
**TRANSGRIPE 1-2 trial design and procedures.** Clinical trial visits are structured in five (or six) time points: initial screening baseline evaluation and administration of the first dose of vaccine in arms A and B (visit 1 and 2), administration in arm B of second dose of vaccine 5 weeks after inclusion (visit 3), short-term follow-up 10 weeks after inclusion (visit 4) and 15 weeks after inclusion (visit 5), as well as long-term follow-up 12 months after the first dose of vaccine (visit 6). Immunogenicity and drug safety were assessed at each programmed time point.

Neutralizing antibody levels for the three influenza strains were measured using microneutralization assays, and seroconversion rates were calculated. Influenza-specific T-cell immune response was measured as the percentage of CD4+ and CD8+ T cells secreting interferon γ in response to influenza stimulation normalized to the negative control.

Clinical trial visits were structured in five (or six) time points as follows:

*Visits 1 and 2*: Patient screening, baseline evaluation and administration of the first dose of vaccine (arms A and B). Protocols for visits 1 and 2 were carried out in one visit when necessary.*Visit 3*: Five weeks after inclusion (range, 25 to 45 days) and administration of the second dose of vaccine (arm B).*Visit 4*: Ten weeks after inclusion (range, 60 to 80 days).*Visit 5*: Fifteen weeks after inclusion (range, 95 to 115 days).*Visit 6*: Twelve months after inclusion (range, 11 to 13 months).

In the programmed visits, patients were prompted to notify the clinician of the onset or continuation of symptoms related to influenza infection occurring during the follow-up period or by email or telephone if symptoms arose during the period between visits. In cases of symptoms, a nasopharyngeal swab was taken for detection of influenza infection using RT-PCR assays.

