A bivariate analysis will be performed to compare primary efficacy outcome, secondary efficacy and safety endpoints between treatment arms of the study. A bivariate analysis using a χ^2^ test or Fisher’s exact test will be used for categorical variables, and the Bonferroni correction will be applied when appropriate. For quantitative variables, the Mann–Whitney *U* test or Student’s t-test based on their distribution will be used. If the variances are not homogeneous (Levene test), the Welch test will be applied (analysis of variance). The relative risks and 95% confidence intervals (95% CI) will be calculated by taking the exponent of the natural logarithm of the mean and 95% CI. Also, the linear trend analysis will be used for multiple comparisons. A multivariate model will be used to adjust for possible confounding variables. The threshold of statistical significance will be set at *P* < 0.05. All reported *P*-values will be based on two-tailed tests. We have optimized the design and conduct of the trial to minimize the number of dropouts and missing data. The analysis will be performed on the ITT population, and missing data will be handled by imputing missingness to failure.

All calculations will be performed using SPSS version 18.0 software (SPSS, Chicago, IL, USA). The TRANSGRIPE1-2 clinical trial has not been programmed with any interim analysis or stopping rules, although the incidence of SAEs is being monitored closely to detect a higher frequency of their occurrence, which may require an early termination of the trial.

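### The primary endpoint has no named strain, visit or success rule, and the trial is sized for one uncorrected test at the 77% strain, so the plan does not secure 5% error and 80% power together

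*Protocol article*

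**What the plan says.** Outcome measures: "Seroconversion rate was the primary end-point variable of the study". Seroconversion is a fourfold rise in titre, and titres are measured against two influenza A strains and one B strain. On timing, "Neutralizing antibody titers were evaluated at 5, 10 and 15 weeks and 1 year after influenza vaccination". No strain, visit or rule for combining strains is singled out.

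The objective is stated in two ways. Abstract: "The primary objective of this trial was to compare short-term and long-term neutralizing antibody immunogenicity of a booster dose". Background: "The primary objective of the present clinical trial is to compare short-term immunogenicity by measuring neutralizing antibodies", with long-term immunogenicity first in the list of secondary objectives.

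Short-term has no fixed meaning either. The abstract applies it to weeks 0, 5, 10 and 15. The Follow-up protocol section calls weeks 5, 10 and 15 midterm. The legend of Figure 1 keeps short-term follow-up for weeks 10 and 15. Visit 3 is "Five weeks after inclusion (range, 25 to 45 days) and administration of the second dose of vaccine (arm B").

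The sample size section reports that in the earlier Spanish study "seroconversion rates against influenza A(H1N1) 2009, influenza A(H3N2) and influenza B were 77%, 67% and 67%, respectively". It then states that "we would expect to achieve 77% and 87% seroconversion rates in the control and experimental arms, respectively" and, with two-sided 5% and 80% power, arrives at 231 evaluable per arm, and 514 in total after 10% dropout. It does not say that H1N1 is the primary strain.

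The Statistical analysis section sets the threshold at P < 0.05 and leaves Bonferroni to be used where appropriate, without defining the family of tests. It adds: "Also, the linear trend analysis will be used for multiple comparisons".

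**The concern.** A primary endpoint that can be read as three or six separate tests has no defined error rate or power until the plan says what counts as success. If any strain at any post-booster visit may carry the claim at P < 0.05, the false-positive chance exceeds 5%. If Bonferroni is applied, the trial was not sized for it. If all three strains must succeed, two of them start from a control rate at which 231 per arm is too few for a 10-point gain. The calculation uses the quoted rate that needs the fewest patients. What is at stake is whether the primary result can be read as the 5%-level, 80%-power test described in the sample size section, and whether strain and visit could be picked after the results are seen.

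**Working it through.** **Inputs from the article.** Control rates 77% (H1N1), 67% (H3N2), 67% (B); gain 10 points; two-sided 5%; 80% power; 1:1; 10% dropout; 231 evaluable per arm.

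**Assumptions not in the article.** The 10-point gain also applies to H3N2 and B. Test statistics share a common correlation ρ, which the article does not give; it is varied from 0 to 0.9.

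**Formulas** (χ² test, pooled variance under the null, no continuity correction), with p̄ = (p1+p2)/2, S0 = √[2p̄(1−p̄)], S1 = √[p1(1−p1)+p2(1−p2)], d = p2−p1:

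- n per arm = (z₁₋α/₂·S0 + z₀.₈·S1)² / d²
- power = Φ[(d√n − z₁₋α/₂·S0) / S1]

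**1. The plan's own figure.** For 77% v 87%: S0 = √0.2952 = 0.5433 and S1 = √0.2902 = 0.5387. n = (1.960×0.5433 + 0.8416×0.5387)²/0.01 = 230.5, so 231. Then 231/0.9 = 256.7, so 257 per arm and 514 in total. Both stated figures reproduce. Power at 231: Φ[(1.5199 − 1.0649)/0.5387] = Φ(0.845) = 80.1%.

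**2. The other two strains.** For 67% v 77%: S0 = √0.4032 = 0.6350 and S1 = √0.3982 = 0.6310. n = 315.3, so 316 per arm; after dropout 316/0.9 = 351.1, so 352 per arm (704 in total). Power at 231: Φ[(1.5199 − 1.2445)/0.6310] = Φ(0.436) = 66.9%.

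This depends on the gain. At 67% v 79%: Φ[(1.8238 − 1.2306)/0.6221] = Φ(0.954) = 83%.

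**3. Bonferroni over three strains** (α = 0.05/3 = 0.0167, z = 2.394), at 231 per arm:

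- 77% v 87%: Φ(0.407) = 65.8%; 308 per arm needed for 80%.
- 67% v 77%: Φ(0.000) = 50.0%; 421 per arm needed for 80%.

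**4. Rules that combine strains.** Joint normal statistics at 231 per arm, single-strain power 80.1%, 66.9% and 66.9%; error rates are under no effect on any strain.

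| | ρ = 0 | ρ = 0.5 | ρ = 0.7 | ρ = 0.9 |
|---|---|---|---|---|
| Power, all three strains at 5% | 36% | 48% | 53% | 60% |
| Power, any strain, uncorrected | 98% | 91% | 88% | 82% |
| Power, any strain, Bonferroni over 3 | 92% | 81% | 75% | 69% |
| Power, H1N1 and H3N2 both at 5% | 54% | 59% | 62% | 65% |
| Chance of ≥1 false positive, 3 tests uncorrected | 14% | 13% | 11% | 8% |
| Chance of ≥1 false positive, 6 tests uncorrected (weeks 10 and 15) | 26% | 21% | 16% | 11% |

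Check at ρ = 0: 0.801 × 0.669 × 0.669 = 0.358; 0.801 × 0.669 = 0.536; 1 − 0.95³ = 0.143; 1 − 0.95⁶ = 0.265.

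**5. Number of tests.** The booster is given at the week-5 visit, so at that visit both arms have had one dose and their comparison cannot show a booster effect. The informative short-term visits are weeks 10 and 15, giving three tests at one visit or six at both.

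**The case against.** The strongest reply is that the stated design is internally sound for one test. 231 per arm does give 80% power for H1N1 at 5%, and Bonferroni over all primary tests would hold the error at 5%. An any-strain rule with Bonferroni would even keep both targets if the strains are only moderately correlated (81% power at 0.5, though 69% at 0.9). The family of tests and their order are also commonly left to the full protocol or SAP, which is not shown. This stands as far as it goes. A reader might infer that neither the 5% nor the 80% holds; the article does not support that, because each can hold under some reading. What it lacks is a statement of which reading applies. The conflict over the primary objective and the sole use of the 77% rate are in the article itself.

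A reader might also count twelve tests (three strains, four visits). That needs 12 months, which the Background section makes secondary, and week 5. Listing week 0 beside week 5 in the abstract suggests a sampling schedule, and no sentence specifies a between-arm primary test at week 5. Three to six is the fair count.

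The 67% power for H3N2 and B rests on a gain of exactly 10 points. The Discussion cites 80% with two doses against 67% with one in liver recipients; a difference of that size would give 89% power at 231 per arm. That comes from a different, limited setting, but it shows the figure is conditional.

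The linear-trend sentence is unclear, but it does not claim to control error, so it is no separate fault. It simply does not supply the missing rule.

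**Conclusion.** The point holds in this form: the article fixes no single primary test, states the primary objective in two incompatible ways, and sizes the trial for one uncorrected 5% test at the quoted control rate that needs the fewest patients. The arithmetic of 231 and 514 is correct. The 80% belongs to H1N1 alone; a stand-alone test of H3N2 or B has about 67%. Depending on the unstated rule, the trial has an error rate above 5% (8 to 14% for three tests, 11 to 26% for six), or less than 80% power on every strain after Bonferroni (66%, 50%, 50%), or 36 to 60% power if all three strains must succeed. These figures assume 231 evaluable per arm, a 10-point gain on each strain and a common correlation of 0 to 0.9. Because this concerns the primary endpoint, it should be settled before unblinded analysis.

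**What to change.** Before any unblinded analysis:

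1. Name one primary strain and one post-booster visit, or state an any-strain or all-strain rule with its alpha allocation. The choice consistent with the existing calculation is H1N1 at a post-booster short-term visit. Other choices can be defended, but one must be written down.
2. Put the remaining strains and visits in a fully specified fixed sequence, or label them secondary. Replace the conditional Bonferroni wording with that rule, and clarify or remove the linear-trend sentence.
3. Treat week 5 as a pre-booster check, not a between-arm efficacy test.
4. Align the abstract with the Background section, with long-term immunogenicity secondary, and use one definition of short-term throughout.
5. Restate power by strain: 80% for H1N1, and about 67% for a stand-alone 5% test of H3N2 or B at a 10-point gain. If the sequence is H1N1, then H3N2, then B, the figures to print are about 54 to 62% for H3N2 and 36 to 53% for B (correlation 0 to 0.7; 65% and 60% at 0.9), not 67%.

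The number of patients does not change, since recruitment is closed. The cost is that strains and visits later in a sequence lose confirmatory status if an earlier test fails. The change is also more than wording: follow-up is complete and the trial is open-label, so the choice must be documented as made blind to results. The blinding of the data analysts makes that possible.

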Efficacy analysis will be performed using seroconversion and seroprotection rates, GMT, GMR and incidence of confirmed influenza infection (to assess clinical effectiveness). The analysis will include, as covariates, previous influenza vaccination, previous record of confirmed influenza infection and other demographic and clinical variables. Additionally, a subgroup analysis will be performed to evaluate effectiveness in patients with decreased response to influenza vaccination (liver failure, use of mammalian target of rapamycin inhibitors, first 6 months posttransplantation).

Vaccination safety analysis will be performed using tabulations of AEs, and descriptive analysis will be provided at baseline and follow-up visits for each treatment group. A tabulation of SAEs will also be provided for each patient within each treatment group. The statistical analysis will be performed by treatment phase (up to 30 days after vaccination) and for the posttreatment phase (long-term follow-up), as appropriate. AEs will be classified on the basis of Medical Dictionary for Regulatory Activities (MedDRA) terminology and summarized for each treatment arm. AE incidence rates will be summarized by system organ class, preferred term, severity and relationship to the IMP. The proportion of patients in each treatment group reporting AEs that occur in ≥3% in each treatment group will be compared using Bayesian methods. The specific system organ classes and preferred terms analyzed will be those reported by at least 5% of the patients in each treatment group.

A bivariate analysis will be performed to compare primary efficacy outcome, secondary efficacy and safety endpoints between treatment arms of the study. A bivariate analysis using a χ^2^ test or Fisher’s exact test will be used for categorical variables, and the Bonferroni correction will be applied when appropriate. For quantitative variables, the Mann–Whitney *U* test or Student’s t-test based on their distribution will be used. If the variances are not homogeneous (Levene test), the Welch test will be applied (analysis of variance). The relative risks and 95% confidence intervals (95% CI) will be calculated by taking the exponent of the natural logarithm of the mean and 95% CI. Also, the linear trend analysis will be used for multiple comparisons. A multivariate model will be used to adjust for possible confounding variables. The threshold of statistical significance will be set at *P* < 0.05. All reported *P*-values will be based on two-tailed tests. We have optimized the design and conduct of the trial to minimize the number of dropouts and missing data. The analysis will be performed on the ITT population, and missing data will be handled by imputing missingness to failure.

All calculations will be performed using SPSS version 18.0 software (SPSS, Chicago, IL, USA). The TRANSGRIPE1-2 clinical trial has not been programmed with any interim analysis or stopping rules, although the incidence of SAEs is being monitored closely to detect a higher frequency of their occurrence, which may require an early termination of the trial.

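### The adverse-event cut-offs must be met in both arms, so the events that differ most between arms drop out of the formal event-level comparison

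*Protocol article*

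**What the plan says.** Two consecutive sentences in the Statistical analysis section of the protocol article set the rule. The first: "The proportion of patients in each treatment group reporting AEs that occur in ≥3% in each treatment group will be compared using Bayesian methods". The second: "The specific system organ classes and preferred terms analyzed will be those reported by at least 5% of the patients in each treatment group". No other place in the article restates either condition as applying to one arm or to any arm.

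The article also promises safety output that carries no cut-off:

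- Just before these sentences: "AE incidence rates will be summarized by system organ class, preferred term, severity and relationship to the IMP".
- For serious events: "A tabulation of SAEs will also be provided for each patient within each treatment group".
- Outcome measures lists the safety endpoints as "rejection episodes, hospitalization, graft loss, mortality, incidence of AEs and severe AEs and rates of discontinuation due to AEs".
- Later in Statistical analysis: "A bivariate analysis will be performed to compare primary efficacy outcome, secondary efficacy and safety endpoints between treatment arms of the study". The methods named there are chi-square or Fisher tests, and relative risks with 95% confidence intervals.

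**The concern.** A frequency cut-off is a normal way to keep an AE comparison readable. It usually admits an event once one arm reaches it. When both arms must reach it, selection depends on the lower of the two rates. Events of similar frequency are kept. For a given booster rate above the cut-off, the rarer the event is after a single dose, the more surely it is left out.

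The safety question in this trial is whether a second dose adds harm. An excess of one specific reaction in the booster arm is the pattern that an event-level comparison should detect, and it is the pattern that this rule removes. Overall AE incidence is a weak substitute, because an excess in one preferred term can be diluted among all the other events.

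**Working it through.** **Inputs from the article**

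- Cut-offs of 3% and 5%, each required in both arms (Statistical analysis).
- Planned size of 257 per arm (Sample size calculation).
- 499 participants enrolled (Trial status), so 499/2 = 249.5, or about 250 per arm.

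**Assumed inputs**

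- True AE rates. The article gives none, so several pairs are shown.
- Patient counts are binomial and independent between arms.

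**Step 1: the plan's own figure.** The cut-offs have no derivation to reproduce. The sample size that sets the denominator does reproduce: 77% v 87%, two-sided 5%, 80% power, no continuity correction gives 231 per arm, and 231/0.9 = 256.7, rounded up to 257.

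**Step 2: cut-offs as patient counts.**

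- 250 per arm: 0.03 × 250 = 7.5, so at least 8 patients; 0.05 × 250 = 12.5, so at least 13.
- 257 per arm: 7.71 and 12.85, so again 8 and 13.

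**Step 3: probability that an event enters the comparison.** Let X_B and X_C be the numbers of patients with the event in the booster and single-dose arms, and r the minimum count.

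- As written: P(both) = P(X_B ≥ r) × P(X_C ≥ r).
- With one arm sufficient: P(at least one) = 1 − P(X_B < r) × P(X_C < r).

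Worked example, 250 per arm, 8% v 1%:

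- 3% rule: P(X_B ≥ 8) = 0.9995 and P(X_C ≥ 8) = 0.0040; product 0.004.
- 5% rule: P(X_B ≥ 13) = 0.967 and P(X_C ≥ 13) = 0.0000019; product about 0.000002.

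| Per arm | Assumed true rates, booster v single | Both arms, 3% rule | Both arms, 5% rule | At least one arm, 5% rule |
|---|---|---|---|---|
| 250 | 8% v 1% | 0.004 | about 0.000002 | 0.967 |
| 250 | 8% v 2% | 0.131 | 0.002 | 0.967 |
| 257 | 10% v 1% | 0.005 | <0.0001 | 0.999 |
| 257 | 10% v 2% | 0.146 | 0.002 | 0.999 |
| 257 | 10% v 3% | 0.507 | 0.048 | 0.999 |

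For comparison, an unfiltered two-sided 5% test with 257 per arm has about 97% power at 10% v 2% and about 90% at 10% v 3%.

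**Step 4: observed counts that the rule would exclude (Fisher exact test).**

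- 20/250 (8.0%) v 3/250 (1.2%): P = 0.0004. Fails both rules, since 3 is below 8 and 13.
- 26/257 (10.1%) v 7/257 (2.7%): P = 0.0009. Fails both rules, since 7 is below 8 and 13.
- 40/257 (15.6%) v 12/257 (4.7%): P = 0.00006. Passes the 3% rule but fails the 5% rule, since 12 is below 13.

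By contrast, 13/250 v 13/250, with no difference at all, passes both rules.

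**The case against.** The strongest reply is that nothing disappears from view. The unfiltered summaries by system organ class and preferred term would show 20 v 3 side by side, and serious events are tabulated. Rejection, hospitalization, graft loss, mortality, discontinuation, and overall and severe AE incidence are compared between arms with no cut-off. This stands. A reader might infer that skewed events go unanalysed altogether, or that the whole safety conclusion is pushed towards no difference. The article does not support that: only the formal event-level comparison is lost.

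Second, both arms receive the same first dose, so familiar vaccine reactions would also occur in the single-dose arm, and near-zero rates there may be untypical. This is fair, and it is why milder pairs are shown. At 10% v 3% the 3% rule keeps the event about half the time, although the 5% rule still keeps it less than 5% of the time.

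Third, the word *each* may be loose drafting for *either*. That is possible, but the wording occurs in both sentences and nothing in the article corrects it. A programmer who follows the text would apply the both-arms filter.

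Two further inferences are tempting and should not be drawn. The 3% and 5% cut-offs need not contradict each other: one governs the AEs compared by Bayesian methods, the other the classes and terms analysed, and they may be two tiers. Their relation is unstated, which calls for clarification. Nor do Bayesian methods for event-level proportions clash with chi-square or Fisher tests of the named safety endpoints, because the two can apply to different quantities. Removing the Bayesian clause would be a matter of preference.

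**Conclusion.** The point holds in limited form. As written, the rule takes out of the formal event-level comparison those AEs that are common in one arm and rare in the other. At 250 per arm and an assumed 8% v 1%, the chance that the event is compared is 0.004 (3% rule) or about 0.000002 (5% rule). At 8% v 2% it is 0.131 or 0.002. With one arm sufficient, the 5% rule would keep either event with probability about 0.97.

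These figures rest on assumed AE rates and on reading *each* literally as both arms. The examples with observed counts need no assumed rates, only that reading. Descriptive AE reporting, the serious-event tabulation, the named safety endpoints and the primary endpoint are untouched. It should be fixed; it does not undermine the trial.

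**What to change.** In both sentences, make the threshold condition apply *in at least one treatment group*. In the 3% sentence the words about each treatment group occur twice; only the second occurrence, which sets the threshold, needs to change. Then either adopt one cut-off or say what each is for, for example which events enter the Bayesian comparison and which classes and terms are analysed.

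The cost is a small change of wording and no new data. The article describes these analyses as still to be done. The price is a longer AE comparison table with more comparisons, and so more chance differences to interpret.
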